**9.1 Definitions**
An adverse event is any adverse change from the patients baseline (pre-Tx) condition, including intercurrent disease(s) occurring during the course of the study after the treatment has started, whether considered related to treatment or not. Treatment includes all agents administered during the course of the study.

Clinical adverse events must be graded on a three-point scale (mild, moderate and severe) and be reported in the appropriate sections of the case record form.

**Mild:** Awareness of symptoms but easily tolerated

**Moderate:** Discomfort enough to interfere with normal activities

**Severe:** Completely prevents normal activities

The relationship between the adverse event and the treatment must also be assessed as follows:

**Definite:** The experience meets the following criteria:

- followed a reasonable temporal sequence from drug administration
- compatible with known drug profile
- abated upon discontinuation of the drug (dechallenge)
- with or without documentation that the experience was confirmed by reappearance of the reaction on repeat exposure (rechallenge)

**Probable:** The experience meets one or more of the following criteria:

- follows a reasonable temporal sequence from drug administration
- compatible with known drug profile and cannot be reasonably explained by the known characteristics of the patient’s clinical state
- with or without documentation that the experience abates upon

discontinuation of the drug (dechallenge)

**Possible:** The experience meets the following criteria:

- follows a reasonable temporal sequence from drug administration
- could have been produced by the patient’s clinical state or by the drug in question
- compatible with known drug profile

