**Definitely Not:**

- The experience is definitely produced by the patient’s clinical state,or by other modes of therapy administered to the patient and not due to the administration of the drug

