**Pre-existing Condition:**

- In this trial, a pre-existing condition (i.e., a disorder present before the adverse event reporting period started and noted on the pre-treatment medical history/physical examination form) should not be reported as an adverse event unless the condition worsens or episodes increase in frequency during the adverse event reporting period.

**9.2 Serious Adverse Event**Any clinical adverse experience or abnormal laboratory test value that is SERIOUS (including life-threatening surgical complications, grave rejection episodes, death), occurring during the course of the study, irrespective of the treatment received, have to be recorded and highlighted in our study database.

A serious adverse event is any untoward medical occurrence that, at any dose:

- Results in death

- Is life-threatening (immediate risk of death as the event occurred)

- Requires in-patient hospitalization or prolongation of existing hospitalization

- Results in persistent or significant disability/incapacity (a substantial disruption in a person´s ability to conduct normal life functions)

- Is a congenital anomaly/birth defect

- Is an overdose (whether by accident or deliberate)

- Is a significant hazard to the patient or requires intervention to prevent a serious outcome.

- Pregnancy will be recorded in the same time frame as serious AEs.

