**9.3 Serious Unexpected Adverse Drug Reaction (ADR)**

A Serious Unexpected adverse drug reaction is defined as reaction which in the opinion of the Investigator is thought to be definitely, probably or possibly drug related and has not previously been known to occur for that drug either from the literature, adverse event listings or Investigator experience - but is not a common clinically insignificant illness.

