**9.4 Follow Up of Adverse Events**

Any abnormal laboratory values, abnormal clinical findings and adverse events which are of clinical significance, in the opinion of the investigator, must be followed with appropriate medical management until resolved.

Individual patients will be excluded from the study if serious adverse effects related to the treatment is observed.

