**10.3 Statistical methods in data analysis**

- The primary evaluation criteria ‘Incidence of rejection’ and ‘Rate of surgical complications’ will be evaluated for several populations:

- All patients who receive at least one dose of study medication, defined as the ‘Intention-to-Treat’ population.

- All patients who complete 12 months of intended study medication, defined as the ‘Intention completed’ population.

The analysis of these categorical parameters will consist of:

1. Comparisons of groups using the Fisher exact test.

2. Confidence intervals of 95% of the percentage of incidence of these

events.

- The loss of grafts and deaths will be analysed by the Kaplan-Meier method for estimating the time to events.
- Continuous (non-categorical) variables will be analyzed by student t-tests and chi-square tests.
- Microdialysis data are typically non-normally distributed. We will therefore use the Wilcoxon Signed rank test for repeated measurements and the Mann-Whitney U test for comparison of groups. We will also use linear mixed model analyses on log10 transformed data for repeated measurements. Receiver operating curves and contingency tables will be used to explore sensitivity and specificity.
- Any other methods that are not planned can be considered as alternative methods.

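### The causality scale in section 9.1 is mis-ordered: timing alone is enough for Probable, while the lower grade Possible needs all three of its criteria

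*Protocol*

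**What the plan says.** Protocol section 9.1 asks the investigator to grade the relationship of every adverse event to treatment, where treatment means all agents given during the study.

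- *Definite* and *Possible* are each introduced by "The experience meets the following criteria", which reads as all of the listed criteria. For *Possible* these are a reasonable time relation to dosing, an event that either the clinical state or the drug could have caused, and compatibility with the known drug profile.
- *Probable*, placed between them, applies when "The experience meets one or more of the following criteria". Its criteria are a reasonable time relation; compatibility with the drug profile together with no reasonable explanation in the patient's clinical state; and a dechallenge line that begins "with or without documentation that the experience abates upon".
- *Definitely Not* covers events definitely produced by the clinical state or "by other modes of therapy administered to the patient and not due to the administration of the drug".

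Section 9.1 does not say which grade prevails when an event fits more than one.

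Two later sections refer to relatedness. Section 9.3 defines a serious unexpected reaction as one "thought to be definitely, probably or possibly drug related and has not previously been known to occur for that drug". Section 9.4 states: "Individual patients will be excluded from the study if serious adverse effects related to the treatment is observed". It does not say which grades count as related.

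**The concern.** A causality scale should become harder to satisfy as the grade rises. Here the step from *Possible* to *Probable* goes the other way, because an event can fail the lower grade and still meet the higher one.

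The setting makes this more than a curiosity. Section 7.1 starts ATG and tacrolimus on day 0, and the flow chart in section 15 shows tacrolimus, MMF and corticosteroids given continuously. Early postoperative events will therefore often bear a plausible time relation to some agent. Section 1.1 reports reoperation in about 30% of earlier patients, and section 2.3 schedules endoscopic and percutaneous biopsies, so procedural complications are to be expected.

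At stake are the causality data recorded for every adverse event, the set of events that section 9.3 treats as drug related, and possibly the exclusion rule in section 9.4. Section 9.2 counts as serious events "including life-threatening surgical complications, grave rejection episodes, death", so events of the kind that make up the primary end-points could come up for a relatedness judgement.

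**Working it through.** The plan gives no figure to reproduce. The check is a count over logical profiles.

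**Inputs, all from section 9.1.** Four yes/no attributes of an event: T, reasonable timing; C, compatible with the known drug profile; X, reasonably explained by the clinical state; D, abated on stopping the drug. That gives 2 × 2 × 2 × 2 = 16 profiles. The second *Possible* criterion (clinical state or drug could have caused the event) is granted as met throughout, which is the widest reading of *Possible*.

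| Grade and reading | Condition | Profiles met | Of these, failing *Possible* |
|---|---|---|---|
| *Definite* | T and C and D | 2 | 0 |
| *Possible* | T and C | 4 | – |
| *Probable* as written, dechallenge line set aside | T, or (C and not X) | 8 + 2 = 10 | 10 − 4 = 6 |
| *Probable* as written, dechallenge line counted | always true | 16 | 16 − 4 = 12 |
| *Probable* with both criteria required | T and C and not X | 2 | 0 |

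**Step 1.** All 4 *Possible* profiles have T, so all 4 also meet *Probable*. *Possible* is never the highest grade met.

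**Step 2.** The 6 profiles that are *Probable* but not *Possible* split into 4 with timing but no fit to the drug profile (T yes, C no) and 2 with fit and no other explanation but no timing (T no, C yes, X no). Among the 8 profiles with timing, *Probable* is met by 8 and *Possible* by 4.

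**Step 3.** The dechallenge line holds with or without documentation, so as a criterion it excludes nothing. Under a rule that any one criterion suffices, it admits every event. The similar line under *Definite*, on rechallenge, does no harm because the other criteria must hold as well.

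**Step 4, an example.** A bleed after a percutaneous pancreas biopsy, soon after a dose, can have T yes and C no. It fails *Possible*, meets *Probable*, and fits *Definitely Not* because another mode of therapy produced it. Nothing in section 9.1 settles the choice.

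**Step 5, use in section 9.3.** That section pools the grades definite, probable and possible. Confusing *Possible* with *Probable* therefore changes nothing there. Only events that fail *Possible* matter. Four of the six such profiles do not fit the drug profile, and such an event may also look like one not previously known for the drug.

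**Step 6, use in section 9.4.** No grade is named, so a link from a *Probable* rating to exclusion is an inference.

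**The case against.** The strongest reply is that the scale guides judgement and is not applied as a truth table. Section 9 records the investigator's opinion on relatedness, and section 9.3 rests on that opinion too. The time relation must be reasonable, which being on continuous tacrolimus does not automatically satisfy. A clearly procedural event has a home in *Definitely Not*, and a doubtful one in *Remote*. Section 9.3 defines a term and attaches no action to it. All of this stands, and it limits the claim to *can be rated* rather than *must be rated*. It does not remove the error: the written rule still ranks the grades wrongly and leaves the overlap unresolved.

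A second reply concerns the remedy. If all three related grades demand fit to the known drug profile, section 9.3 could have few or no unexpected reactions left to capture. This is partly right. Being compatible with a profile is not the same as having been seen before, but the wording should leave room for a plausible new reaction.

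A reader might infer something stronger: that patients with surgical complications would be rated as drug related, excluded under section 9.4, and have later rejections missed, biasing the comparison with the historical controls. The documents do not support this. Section 9.4 names no grade. The end-points in section 10.1 are biopsy-proven rejection, and reoperation or reintervention, with no causality requirement. The stopping criteria in section 10.4 use rates, and no analysis in section 10.3 uses a relatedness grade. The Intention-to-Treat population is "All patients who receive at least one dose of study medication", so an excluded patient stays in it. Section 8 requires biopsies in all suspected rejections, and section 11.1 asks for retrievable data on patients who withdraw. Any estimate of lost rejections or added sample size would need shares that the protocol does not give.

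**Conclusion.** Wrong as written; minor. The grade *Probable* is easier to meet than *Possible*: 6 of the 10 profiles that meet it fail the lower grade, or 12 of 16 if the dechallenge line is counted. This rests on two readings: that the introduction to *Possible* means all of its criteria, and that its second criterion is granted. The counts describe the logic of the rule. They do not say how often an investigator would misrate an event, and the protocol gives no basis for estimating that.

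The demonstrated consequence is a distorted causality record and a drug-related set in section 9.3 that can include events failing every sensible test of relatedness except timing. An effect through section 9.4 is possible but inferred. Bias in a primary end-point or a planned analysis is not shown.

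**What to change.** Change section 9.1 as follows.

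1. *Probable*: require all of (1) a reasonable temporal sequence and (2) an event that is compatible with the known drug profile or pharmacologically plausible, and not reasonably explained by the patient's clinical state, surgery or a procedure. Keep dechallenge as a remark, not a criterion.
2. *Possible*: use the same phrase, compatible or pharmacologically plausible, so that section 9.3 can still capture unexpected reactions.
3. Precedence: state that one rating is given, the highest whose criteria are all met, and that *Definitely Not* takes precedence when surgery or a procedure clearly produced the event.

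With these changes no profile is *Probable* without also being *Possible*. They do not settle which grades trigger exclusion under section 9.4; that wording stays as it is.

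Cost: a few wording changes and one re-read of events already rated *Probable*. No new visits, samples or patients are needed.

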**Remote:**

- It is not likely to be any reasonable association between the drug and the observed experience

**Definitely Not:**

- The experience is definitely produced by the patient’s clinical state,or by other modes of therapy administered to the patient and not due to the administration of the drug

**Unknown:**

- Information provided is insufficient for a confident drug relationship to be classified

**Pre-existing Condition:**

- In this trial, a pre-existing condition (i.e., a disorder present before the adverse event reporting period started and noted on the pre-treatment medical history/physical examination form) should not be reported as an adverse event unless the condition worsens or episodes increase in frequency during the adverse event reporting period.

**9.2 Serious Adverse Event**Any clinical adverse experience or abnormal laboratory test value that is SERIOUS (including life-threatening surgical complications, grave rejection episodes, death), occurring during the course of the study, irrespective of the treatment received, have to be recorded and highlighted in our study database.

A serious adverse event is any untoward medical occurrence that, at any dose:

- Results in death

- Is life-threatening (immediate risk of death as the event occurred)

- Requires in-patient hospitalization or prolongation of existing hospitalization

- Results in persistent or significant disability/incapacity (a substantial disruption in a person´s ability to conduct normal life functions)

- Is a congenital anomaly/birth defect

- Is an overdose (whether by accident or deliberate)

- Is a significant hazard to the patient or requires intervention to prevent a serious outcome.

- Pregnancy will be recorded in the same time frame as serious AEs.

**9.3 Serious Unexpected Adverse Drug Reaction (ADR)**

A Serious Unexpected adverse drug reaction is defined as reaction which in the opinion of the Investigator is thought to be definitely, probably or possibly drug related and has not previously been known to occur for that drug either from the literature, adverse event listings or Investigator experience - but is not a common clinically insignificant illness.

**9.4 Follow Up of Adverse Events**

Any abnormal laboratory values, abnormal clinical findings and adverse events which are of clinical significance, in the opinion of the investigator, must be followed with appropriate medical management until resolved.

Individual patients will be excluded from the study if serious adverse effects related to the treatment is observed.

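### Section 9.4 lets a serious treatment-related event end study participation, with no assurance that outcome follow-up continues, and the 12-month completer set used for both primary criteria can understate event rates in the prospective cohort

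*Protocol*

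**What the plan says.** - **Exclusion (protocol 9.4).** "Individual patients will be excluded from the study if serious adverse effects related to the treatment is observed". The rule concerns leaving the study, not only stopping a drug. It does not say whether endpoint follow-up continues.
- **What is serious (9.2).** The description covers events "including life-threatening surgical complications, grave rejection episodes, death", and the criteria add prolonged hospitalisation.
- **What is treatment (9.1).** "Treatment includes all agents administered during the course of the study".
- **Follow-up (section 4).** It runs to at least 60 months, or until the patient discontinues participation.
- **Data on leavers (11.1).** Incomplete case report forms must be submitted, with retrievable data on patients who withdrew. Continued endpoint assessment is not required.
- **Analysis sets (10.3).** The two primary criteria, rejection and surgical complications, "will be evaluated for several populations". The 'Intention-to-Treat' set is "All patients who receive at least one dose of study medication". The 'Intention completed' set is "All patients who complete 12 months of intended study medication". Neither is named as primary. The analysis is "Comparisons of groups using the Fisher exact test" with 95% confidence intervals.
- **Controls (2.1).** They are a retrospective group transplanted in 2011-2013 (the historic controls, HC). The protocol does not say how either set is formed for them.

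**The concern.** Whether a patient stays in the study depends partly on outcome, and the outcomes involved overlap the primary endpoints. The relatedness condition in 9.4 narrows the rule, but not by much. Treatment means every agent given, the 'possible' grade in 9.1 admits events that the patient's clinical state could also explain, and section 2 itself proposes that corticosteroids contribute to complications and reoperations.

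An investigator's decision during this study cannot have been applied to retrospective controls, so any loss through 9.4 falls on the prospective cohort (SCOS) alone. Uncounted failures there make the reduced-steroid regimen look better. Section 10.1 names overlooking a raised SCOS rejection rate as the main error to avoid, so the bias runs in the direction the plan most wants to guard against.

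The completer set is a second route. Section 1.1 reports significantly more rejection among patients who lost grafts, so a set that sheds early failures may also shed rejections.

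**Working it through.** The plan gives no figure for exclusions or for the size of either set, so there is none to reproduce on this point. The rates below come from section 10.2: a reference rate of 0.30 and a rejection rate to be detected of 0.40. They reproduce the stated requirement: (0.30×0.70 + 0.40×0.60) × 7.9 / 0.10² = 355.5, printed as 355 per arm. That figure is not affected by this point.

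**Step 1: the passages side by side.** Section 9.4 takes the patient out of the study, section 4 lets follow-up stop when participation stops, and section 11.1 recovers only what happens to be retrievable. Followed as written, the plan can lose later endpoint events. It does not state that they will be lost.

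**Step 2: at-least-one-dose set.** Both primary endpoints are the fraction of patients with one or more events (2.1, 10.1). A patient excluded because of a grave rejection has therefore already counted for rejection, and further rejections would change nothing. What can be missed:

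- a first event of the other primary endpoint, such as a first reoperation after exclusion for rejection;
- a first rejection or reoperation after exclusion for some other serious event, such as an infection;
- graft loss and death up to 60 months, where exclusion would act as informative censoring in the Kaplan-Meier analysis.

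With 60-80 patients, each uncounted first event lowers the SCOS rate by 1/80 = 1.25 to 1/60 = 1.67 percentage points.

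**Step 3: completer set.** Let p be the true SCOS rate and f the fraction of event patients who drop out of the set. Assume for now that no event-free patient leaves. Then

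observed rate = p(1−f) / (1−pf).

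| f (assumed) | p = 0.30 | p = 0.40 |
|---|---|---|
| 10% | 0.27/0.97 = 27.8% | 0.36/0.96 = 37.5% |
| 20% | 0.24/0.94 = 25.5% | 0.32/0.92 = 34.8% |
| 30% | 0.21/0.91 = 23.1% | 0.28/0.88 = 31.8% |
| 50% | 0.15/0.85 = 17.6% | 0.20/0.80 = 25.0% |

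A true 40% would look equal to a 30% control rate at f = 0.10/0.28 = 35.7%, which is 0.40 × 0.357 = 14.3% of the cohort.

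**Step 4: event-free patients leave too.** With a fraction g of event-free patients leaving,

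observed rate = p(1−f) / [p(1−f) + (1−p)(1−g)].

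For p = 0.40 and f = 30%:

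- g = 0: 31.8%
- g = 10%: 0.28/(0.28+0.54) = 34.1%
- g = 15%: 0.28/(0.28+0.51) = 35.4%
- g = 30%: 0.28/(0.28+0.42) = 40.0%, no bias

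The bias depends on the difference between f and g, and would reverse if g exceeded f.

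**Step 5: effect on the Fisher test in the completer set.** This adds three assumptions: 80 patients in each group at the start, g = 0, and no filter on HC, whose rate is 0.30. The probabilities are by exact enumeration, two-sided 5%.

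| f | Significant result favouring SCOS, true rates 0.30 and 0.30 | Doubling detected, true rates 0.60 and 0.30 |
|---|---|---|
| 0 | 1.7% | 95.9% |
| 10% | 4.1% | 92.5% |
| 20% | 7.4% | 85.7% |
| 30% | 13.8% | 72.0% |
| 50% | 38.1% | 30.4% |

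With 60 per group, the first column runs from 1.5% to 28.6% and the second from 89.4% to 22.5%.

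**The case against.** A reader might infer that the worst outcomes simply vanish from SCOS while the controls lose none. The protocol does not support that, for these reasons:

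- Section 10.3 already lists a set that keeps every patient with at least one dose, and there the event that triggers exclusion has been counted.
- Only effects judged related to treatment trigger 9.4. A purely technical leak, or a rejection put down to too little drug effect, may not qualify.
- Section 9.4 does not say that follow-up stops. It requires clinically significant adverse events to be managed until resolved, and 11.1 asks for retrievable data.
- That controls lose none is certain only for 9.4. The protocol is silent on whether the 12-month completer restriction would also be applied to HC. If it were, HC would shed early failures too.
- Nothing says that a rejection ends the intended medication. Section 8 describes treating rejection, not stopping maintenance.

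All of this stands and limits the size of the problem. It is also fair that the choice of primary set, and its construction for controls, might be settled in an analysis plan that is not at hand.

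What does not fall away is the 9.4 rule itself. It is stated, it depends on outcome, it works on one group only, and it leaves endpoint follow-up open. An analysis plan cannot restore outcome data that were never collected. Nor is retrievable data on withdrawn patients the same as planned assessment to 60 months.

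**Conclusion.** The point holds in limited form and should be fixed. Read with sections 4 and 11.1, section 9.4 can lose later endpoint events in the prospective cohort through a rule that never operated on the controls. In the at-least-one-dose set the exposure is modest for the primary endpoints, at 1.25 to 1.67 points per missed first event. It matters more for graft and patient survival up to 60 months. In the completer set the bias can be larger: a true 40% reads as 37.5% to 25.0% over the assumed range of 10% to 50%.

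Those fractions have no source in the protocol. They assume that no event-free patient leaves, and the test probabilities further assume equal group sizes and an unfiltered HC. A reader might take them as showing that a true increase in rejection would be erased. They show only that this could happen in the completer set under heavy and selective exit. The result does not carry over to the at-least-one-dose set.

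**What to change.** Reconcile sections 4, 9.4, 10.3 and 11.1:

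1. **9.4, 4 and 11.1.** State that a serious related event does not end outcome follow-up or remove the patient from analysis. Rejection, reoperation, graft loss and death are recorded to 60 months unless consent is withdrawn. Decisions on treatment and on study-specific procedures, such as the added percutaneous biopsies, stay with the treating team. No clinical rule is proposed here.
2. **10.3, primary set.** Name the at-least-one-dose set as the basis for the primary comparison with HC, and apply it to all transplanted controls. Section 7.1 starts ATG and tacrolimus before surgery, so counting every transplanted control is the natural counterpart.
3. **10.3, completer set.** Label the 12-month completer set supportive.

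The cost is a few sentences and slightly more follow-up of patients who would otherwise have left. The visits are already in the flow chart in section 15.
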